**Figure 2 figure2:**
[figure not shown]
Flow diagram of prospective recruitment and follow-up. INR: international normalized ratio. War-PATH: Warfarin Anticoagulation in Patients in Sub-Saharan Africa.

**Table 1 table1:** Participant groups.

	Prospective	Retrospective
Population	Participants starting warfarin and consenting to implementation bundle	Historical controls started on warfarin at anticoagulation clinics where warfarin bundle is implemented
Sample size	152	330
Inclusion criteria	New initiators on warfarin Indication for warfarin is VTE^a^, AF^b^, or VHD^c^ Adults (ie, 18 years or older) Participant is resident in and willing to be followed up at a health facility where follow-up is feasible	New initiators on warfarin Indication for warfarin is VTE, AF, or VHD Adults (ie, 18 years or older)
Exclusion criteria	Pregnancy Received more than one dose of warfarin prior to recruitment Diagnosed with and currently on treatment for Tuberculosis	Pregnancy Diagnosed with and treated for Tuberculosis at time of warfarin initiation
Self-reported ethnicity	Yes	No
EQ-5D-3L questionnaire	Yes	No
Participant expenses tool	Yes	No
Baseline INR^d^	Yes	Yes
INRs during the first 3 months of treatment	Yes	Yes
All adverse events	Yes	Yes
Hospital admissions	Yes	Yes

^a^VTE: venous thromboembolism.

^b^AF: atrial fibrillation.

^c^VHD: valvular heart disease.

^d^INR: international normalized ratio.

#### Retrospective Review of Patients’ Clinical Records

The following data will be collected from clinical records: age, sex, weight, indication for anticoagulation, target INR range, HIV status, recruitment center, all INR measurements during the first 3 months, any dose changes, and any hospitalizations or adverse events. If participants in the retrospective review were initially hospitalized and then discharged, the recruitment hospital site clinical records as well as the clinical records at the referral clinic will be reviewed.

### Withdrawal Criteria

A participant can withdraw from the study at any time if it is his or her wish or if it is medically necessary, as judged by the Investigator. A participant will be withdrawn if any of the following applies:

Voluntary discontinuation by the participant, who is at any time free to discontinue their participation in the study without prejudice to further treatment.Incorrect enrollment of the participant (ie, the participant does not meet the required inclusion and exclusion criteria).Participant fails to comply with the protocol requirements or fails to cooperate with the investigator.Participants experiencing severe adverse events who return to standard care.

### Sample Collection

Two tubes of blood (10 or 12 ml total) will be collected in ethylenediaminetetraacetic acid (EDTA) tubes and used for DNA extraction. The EDTA blood sample will be stored at either –20 C or –80 C. One tube will be shipped to the United Kingdom, and 1 kept in Cape Town or Kampala. DNA will be extracted from the EDTA sample at the Wolfson Centre for Personalised Medicine in Liverpool. We will seek ethical approval from the University of Cape Town HREC/Joint Clinical Research Centre Institutional Review Board Office, Kampala, for any future use.

### Adverse Events

The decision to start warfarin will already have been made by participants’ clinical teams before enrollment. We will capture warfarin-related adverse events as part of the secondary outcome measures. A blood test to obtain DNA may sometimes lead to bruising at the site of venepuncture, but all blood will be taken by trained and experienced staff. All adverse events will be recorded and appropriately reported. Investigators will assess whether adverse events were related to warfarin using the Liverpool Adverse Drug Reaction Causality Assessment Tool [12].

### Cost-Effectiveness

We will perform a cost-effectiveness analysis to judge whether the warfarin bundle represents good value for money. These will be based on estimated costs associated with warfarin treatment and health outcomes expressed as QALYs and disability-adjusted life years (DALYs). Resource use will include hospital admissions, outpatient clinic visits, phlebotomy, Point-of-Care and laboratory INR tests, additional blood tests, and prescribed warfarin. External data (which may require extrapolation from other studies or countries) may be required to estimate the costs of managing rare adverse events, including strokes and major bleeds. Unit costs will be identified from a number of sources, including the Western Cape Department of Health (eg, Uniform Patient Fee Schedule), the Ugandan Joint Medical Stores catalog, and the World Health Organization “Choosing Interventions that are Cost-Effective” (WHO-CHOICE) model for estimating unit costs for hospitalizations [13]. Patients will be asked to complete the EQ-5D-3L to estimate health utilities at the initial visit and 1 follow-up visit and to complete a questionnaire to record out-of-pocket costs by telephone. The economic analysis will estimate the incremental costs per QALY gained and DALY averted and inform policy.

### Study Outcomes

The primary outcome for this study is TTR over the initial 3 months of warfarin therapy, which we will measure using the Rosendaal linear interpolation method [14]. We will compare time in the therapeutic INR range between the prospectively followed participants who receive the warfarin bundle and a retrospectively reviewed patient group. This will yield an estimate of the impact of the warfarin care bundle as a whole. It will not be possible to distinguish the effect of the individual components of the warfarin bundle on TTR.

The secondary outcomes include time to achieve therapeutic INR and number of adverse events (death, bleeding, or thrombosis), which will be compared between the prospectively followed-up participants and the retrospectively reviewed patient group. We will also explore staff and patient experiences and acceptability of the warfarin bundle using in-depth interviews or focus group discussions and conduct an economic analysis of the cost-effectiveness of the warfarin bundle. In addition, we will perform a qualitative assessment of useful lessons from the RCA.

### Patient and Public Involvement

Patients or the public will not be involved in the design, conduct, or reporting of this study. However, where possible, study findings will be disseminated through public and patient engagement activities.

### Data Analysis Plan

For the prospective and retrospective studies, all statistical analyses will be undertaken in R. For determining percentage time in target range for each participant, all INR measurements during the first 12 weeks as well as the first INR measurement after the 12-week time point will be used, and the method of Rosendaal et al [14] will be applied. Percentage TTR will be compared between the prospective implementation group and the retrospective standard of care group using the Student *t* test. Time to achieving target INR (defined as the first of at least two INR measurements in range at the same dose) will be compared between the prospective and retrospective groups using the log-rank test (to compare the survival distributions of the 2 groups, and these will be calculated using the Kaplan-Meier estimator). Adverse events will be compared between the 2 groups using a chi-square test. A significance threshold of *P*<.05 will be applied.

The primary analysis will include all participants who remain in the project for at least 2 weeks (14 days). Our primary analysis will include only patients who have at least two weeks’ follow-up, since it is unlikely that those with less than 2 weeks’ follow-up will have sufficient information on INR measurements for TTR to be reliably estimated. A sensitivity analysis will be undertaken, including only participants who have completed 12 weeks (84 days) of follow-up.

We will also conduct both an intention-to-treat analysis (including all recruited patients) and a per-protocol analysis (excluding patients where health care provider decided to reject the dose recommended by the dosing algorithm). The project will follow national guidelines for best practice and be guided by local policy. Relevant data will be made openly available to other researchers in a timely way (after primary outputs are published) with as few restrictions as possible unless we are protecting intellectual property, respecting confidentiality, or honoring third-party agreements. The program management board will review access to data and will provide a governance mechanism.

We will perform a secondary analysis comparing the primary and secondary outcomes between retrospective controls from the pre–COVID-19 and COVID-19 periods to measure the impact of the pandemic on anticoagulation control.

Total direct costs will be calculated for each patient over the course of the 12 weeks. Utilities will be estimated from the administration of the EQ-5D-3L questionnaire (available in 8 languages spoken in South Africa and 2 in Uganda) and valued using the Zimbabwean value set, as none exist for these countries [15]. Regression analyses using transformed utility (or cost) as the dependent variable and controlling for clinical and demographic factors will be used to estimate the association between health utility (or cost) and TTR. These will be incorporated in a decision analytic model, also populated with data from evidence on the relationship between TTR and health outcomes (strokes, hemorrhagic events, etc), to estimate overall costs and QALYs.

In accordance with World Health Organization recommendations, the number of DALYs, expressed as the collective number of years lost due to ill health, disability, or early death, will be calculated by adding the adjusted number of years lived with disability and the number of years of life lost due to premature mortality. The years lived with disability component represents a duration that is scaled by disability severity weights that range from 0 (no adverse impact on quality of life) to 1 (burden equivalent in preference to being dead). Weightings will be applied to time with disability based on disease areas [16] and DALYs for individuals will be calculated and used as an alternative metric of cost-effectiveness (cost per DALY averted).

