## Methods

### Study Design and Setting

This is a mixed methods implementation study of patient- and process-centered activities to improve the quality of anticoagulation in Sub-Saharan African patients involving 3 hospitals in Kampala, Uganda (Mulago National Referral Hospital, Uganda Heart Institute, and Kiruddu National Referral Hospital) and 2 hospitals in Cape Town, South Africa (Groote Schuur Hospital and Tygerberg Hospital).

The general study design is described in Figure 1.

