#### Staff Training

We will include co-design workshops discussing the rationale for the bundle and likely implementation issues with a team of clinicians involved in the provision of anticoagulation services. Training will be personalized based on local requirements, depending on the site and staff involved.

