### Sample Size and Power Calculations

To calculate our sample size, we assumed TTR in current practice to be 0.41 (based on average TTR from our audit) and the SD of TTR to be 0.25 on the basis that anticoagulation control before implementing the bundle is better than that found during the audit (0.33), due to the introduction of the clinical algorithm in a preceding pilot implementation study. We also assumed a Type I error rate of 0.05, power of 80%, and that the retrospective and prospective ratio would be 2:1. To achieve a minimum clinically important difference of 0.07 (ie, improvement from 43% to 50% TTR), we calculated that we would need at least 304 retrospective and 152 prospective participants (including a 10% contingency for losses to follow-up). This is in total across both Uganda and South Africa.

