## Discussion

### Overview

This protocol will evaluate the implementation of the “warfarin bundle,” a group of interventions aiming to improve the quality of warfarin anticoagulation in SSA. Given the complex and multifaceted challenges contributing to suboptimal anticoagulation in these populations, a mixed methods protocol, including both patient-centered and process-centered activities, was designed.

The study design has several limitations, primarily relating to the complexity of the population, the challenges of investigating anticoagulation in this particular setting, and the selection of a bundle of interventions, including patient and provider education, rather than a single intervention.

In Uganda, anticoagulation services are centralized in Kampala, and there are no control clinics that could be run concurrently in a cluster randomized trial design; within South Africa, selection of appropriate control clinics would necessitate involving another city in addition to Cape Town, thereby bringing unfeasible logistic challenges and cost. Therefore, a before-and-after design was considered most appropriate. We have shown in the preceding Audit study that we can get high-quality data from the case notes [3].

An eligibility criterion for participants in the prospective evaluation is their willingness and ability to comply with study procedures. In practical terms, this excludes individuals who travel long distances from peripheral regions of Uganda to the tertiary facilities where anticoagulation is accessed; this may mean that the participants in the retrospective and prospective arms are not perfectly matched in terms of socioeconomic status. However, the recruitment sites are in the area of highest population density, and the majority of individuals in both the retrospective and prospective arms are anticipated to reside within Kampala and the surrounding Wakiso district.

Through the selection of a bundle of interventions, it will not be possible to attribute improvement to a single element of this. However, this is a complex patient group requiring holistic care, and several important areas have been identified for improvement. The health, economic, and qualitative aspects of the protocol are designed to evaluate the benefits of the bundle as a whole.

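### The sample size and the primary t test ignore hospital, so the 5% error rate and 80% power hold only with a similar hospital mix in both periods and no hospital-by-period variation in TTR

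*Protocol article*

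**What the plan says.** Study Design and Setting describes a study "involving 3 hospitals in Kampala, Uganda (Mulago National Referral Hospital, Uganda Heart Institute, and Kiruddu National Referral Hospital) and 2 hospitals in Cape Town". Table 1 takes the historical controls from the clinics that later implement the bundle, so each hospital contributes a before and an after group.

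Part of the bundle works through the clinic: staff training, root-cause findings fed back to clinic staff, and point-of-care INR testing. Under Staff Training: "Training will be personalized based on local requirements, depending on the site and staff involved".

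Sample Size and Power Calculations assumes a "Type I error rate of 0.05, power of 80%, and that the retrospective and prospective ratio would be 2:1", takes "the SD of TTR to be 0.25", and targets a "minimum clinically important difference of 0.07 (ie, improvement from 43% to 50% TTR"). From this, "we calculated that we would need at least 304 retrospective and 152 prospective participants (including a 10% contingency for losses to follow-up"), in total over both countries. No intracluster correlation, design effect or site term appears.

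The Data Analysis Plan fixes the primary comparison: "Percentage TTR will be compared between the prospective implementation group and the retrospective standard of care group using the Student" t test, at P<.05. Time to target INR is compared by a log-rank test with no stratification stated. Recruitment center is on the data list of both groups but is used in neither analysis.

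The Discussion says for Uganda that "there are no control clinics that could be run concurrently in a cluster randomized trial design" and chooses a before-and-after design. Its limitations do not mention clustering by hospital.

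**The concern.** A two-sample t test on patients takes its standard error from patient-to-patient variation alone. Hospital can upset this in two ways.

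- **Shift in mix.** If hospitals differ steadily in TTR and contribute different shares before and after, part of the difference in means is a difference in case source.
- **Hospital-by-period variation.** If TTR at a hospital moves between periods for its own reasons (staff, clinic schedule, INR turnaround), that movement enters the estimate but not the standard error. With five hospitals it averages out slowly.

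In either case the interval is too narrow and P<.05 is reached too often with no bundle effect. The 80% power also assumes that neither source exists. The results are meant to inform a larger multisite trial, for which variation between hospitals is a needed design input that a pooled test hides.

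**Working it through.** **Inputs from the protocol:** SD 0.25; difference 0.07; alpha 0.05 (taken as two-sided, since no side is stated); power 80%; ratio 2:1; 304 and 152 patients; five hospitals.

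**Assumed, because the protocol gives no value:** ICC, the share of TTR variance due to hospital in a given period; CAC, the fraction of that hospital component shared by both periods; equal hospital sizes unless stated.

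**Step 1. Reproduce the plan's figure.** For independent patients at 2:1, the retrospective n = 3 × (1.960 + 0.842)² × 0.25² / 0.07² ≈ 300.3, so 301, and 151 prospective. At 304 and 152:

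- 1/304 + 1/152 = 0.009868
- SE = 0.25 × √0.009868 = 0.0248
- power = Φ(0.07/0.0248 − 1.96) = 80.5%

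The stated size is thus the independent-patient size, with no allowance for hospital. (Nor does it leave room for the stated 10% loss, which is a separate point.)

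**Step 2. Add hospital-by-period variation.** With five equal hospitals the shared part of the hospital effect cancels, leaving

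Var(difference)/SD² = 2 × ICC × (1 − CAC)/5 + (1 − ICC) × 0.009868.

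The true type I error of the planned test is 2 × [1 − Φ(1.96/√ratio)], where ratio is this variance over 0.009868. Example, ICC 0.05 and CAC 0.8: 0.004 + 0.009375 = 0.013375; ratio 1.355; 1.96/1.164 = 1.684; error 9.2%. The correct SE is 0.25 × √0.013375 = 0.0289, and power at a normal critical value is Φ(0.07/0.0289 − 1.96) = 68%.

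| ICC | CAC | Variance ratio | Type I error of planned test | Power, correct SE, normal critical value | Power, paired t on 5 differences (4 df) |
|---|---|---|---|---|---|
| 0 | – | 1.00 | 5.0% | 80% | 57% |
| 0.02 | 0.9 | 1.06 | 5.7% | 78% | 55% |
| 0.02 | 0.8 | 1.14 | 6.7% | 75% | 52% |
| 0.05 | 1 | 0.95 | 4.4% | 82% | 59% |
| 0.05 | 0.9 | 1.15 | 6.8% | 75% | 51% |
| 0.05 | 0.8 | 1.36 | 9.2% | 68% | 45% |
| 0.05 | 0.5 | 1.96 | 16.2% | 52% | 34% |
| 0.05 | 0 | 2.98 | 25.6% | 37% | 24% |

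Simulation (20,000 runs per setting) at ICC 0.05 and CAC 0 gave 26.1% against 25.6%.

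**Step 3. Shift the hospital mix, with stable hospital effects (CAC 1).** Let controls be 20% per hospital and bundle patients 40/30/15/10/5%. The squared differences in share sum to 0.04 + 0.01 + 0.0025 + 0.01 + 0.0225 = 0.085. At ICC 0.05 the variance is 0.05 × 0.085 + 0.95 × 0.009868 = 0.013625, and the t test's type I error is 9.5%. In simulation (8,000 runs) the t test gave 9.8% and a linear model with hospital as a fixed effect gave 5.0%.

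**Step 4. What hospital adjustment does not cover.** With equal mix and ICC 0.05, the hospital fixed-effect model with its ordinary standard error still had a simulated type I error of about 10% at CAC 0.8 and 17% at CAC 0.5.

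**Step 5. Could more patients cure it?** The first variance term does not shrink with n. For 80% power the total variance must not exceed (0.07/2.802)² = 0.000624. The hospital-by-period part alone is 2 × 0.0625/5 × ICC(1 − CAC) = 0.025 × ICC(1 − CAC), which reaches that limit when ICC(1 − CAC) is about 0.025.

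**The case against.** The strongest case on the other side has four parts.

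- **Exposure is not wholly clinic-level.** A reader might infer that the bundle is assigned to the clinic and that the contrast rests on just five hospital differences. The documents do not support this. Table 1 defines the prospective group by consent to the bundle; algorithm dosing, counselling, text messages and study-driven INR checks reach enrolled individuals; discharged patients may be followed at referral clinics. This stands. Patients remain grouped by hospital all the same, and some components do act on the clinic.
- **Hospital-by-period variation is not documented.** The Introduction's remark on differing clinic practices describes differences between clinics. If these are constant over time and the mix is similar, the t test is slightly conservative (4.4% at ICC 0.05). A reader might infer that the real false-positive rate is known to exceed 5%; the protocol gives neither ICC nor CAC, so this is conditional. Change over time is contemplated, through the earlier pilot algorithm and the planned pre–COVID-19 versus COVID-19 comparison, but not shown to differ by hospital.
- **A cluster-aware primary analysis is costly.** A reader might conclude that a random hospital-by-period model must replace the primary test. With five hospitals the paired analysis has 57% power even without clustering. Treating these five hospitals as fixed is a legitimate target. Because group and period coincide, the random term would also absorb real site differences in bundle effect. This stands, and it places that model in a sensitivity analysis.
- **Common drift is untouched.** A trend shared by all hospitals biases the comparison whichever standard error is used. That is true, but it is no reason to ignore hospital.

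**Conclusion.** The concern holds in conditional form. The protocol fixes a sample size and a primary test that both treat patients at five hospitals as independent, while recruitment center is recorded and unused. Nominal 5% error and 80% power need two conditions: similar hospital mix in both periods, and no hospital-by-period variation.

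Under assumed ICC 0.02 to 0.05 and CAC 0.8 to 0.9, with equal hospitals, type I error is about 6% to 9% and power about 68% to 78% at a normal critical value. At lower CAC it is worse (16% and 52% at ICC 0.05, CAC 0.5). With a marked shift in mix and stable hospital effects at ICC 0.05, the planned test errs about 10% of the time and a hospital-adjusted model 5%. All these figures rest on assumed ICC, CAC and hospital shares; the documents do not show that the planned test is invalid in this study.

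**What to change.** 1. **Data Analysis Plan, primary outcome.** Estimate the TTR difference from a linear model with group and hospital as fixed effects. Stratify the log-rank test for time to target INR by hospital. The Student t test can stay as a labelled unadjusted result.
2. **Data Analysis Plan, sensitivity analysis.** Report the five hospital-specific before-after differences with a cluster-aware interval: either a hospital-by-period random effect with a small-sample correction, or a paired t test on the five differences (4 df). Say that hospital adjustment and stratification do not cover hospital-by-period drift, and that this sensitivity analysis has low power with five hospitals.
3. **Sample Size and Power Calculations.** State that 80% power assumes independent patients with no hospital-by-period variation, and show power over a range of ICC and CAC, as in the table above.

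Cost: no new data or patients, since recruitment center is already collected in both groups. The sensitivity interval will be wider and the stated power less favourable. The article reports that recruitment ended in August 2022 and that analysis was underway by February 2023, so the change should be dated and reported as made at that stage. None of it removes a secular trend common to all hospitals, which should be stated as a remaining limitation.

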### Participant Recruitment

#### Prospective Study

We will recruit participants for whom a decision has already been made to initiate warfarin by the managing clinician (Figure 2). Decisions regarding whether or not patients require inpatient management for the initiation of warfarin are also made by the managing clinician. Participants who meet the inclusion criteria will be consecutively screened and enrolled in the study. In cases where participants are discharged from the hospital and referred for follow-up in a clinic close to their home or in the outpatient clinic of the hospital, the clinical records used at the recruitment site and those at the referral clinic will be reviewed.

The participant’s first 3 days of dosing will be driven by our new algorithm (Multimedia Appendix 1). Thereafter, dose revisions will be made according to current guidance outlined in the “Standard Treatment Guidelines and Essential Medicines List for South Africa” [11]. We will repeat the INR of participants every 2-4 days until stability is reached (2 consecutive INRs are in the target range). We will ensure close monitoring during the first 14 days of treatment. If stability is reached before the 14th day, we will continue to closely monitor the patient for the first 14 days. If the participant has not reached stability at 14 days, we will continue to monitor the participant with INRs every 2-4 days and adjust the warfarin dose until stability is reached. As we measure participants’ INR every 2-4 days over this period of close follow-up, we will propose dose adjustments to the clinical team based on INR results. The clinical team will still be free to override proposed adjustments based on their clinical expertise. Once stability is reached, we will perform one more INR 1 week later, after which the participants’ care will be fully handed back to the clinical team, and participants will continue to follow-up according to the local standard of care. We will continue to monitor and record all consecutive INR results for 3 months through direct contact with the participant at outpatient clinic, home visits, or electronic or paper record review.

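### Time to target INR is compared by log-rank although the groups need not be tested equally often, so a significant result could not separate faster control from earlier detection

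*Protocol article*

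**What the plan says.** Study Outcomes in the protocol article lists the endpoint: "The secondary outcomes include time to achieve therapeutic INR". It is also the first secondary aim under Objectives.

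The Data Analysis Plan fixes both definition and test. The definition reads: "Time to achieving target INR (defined as the first of at least two INR measurements in range at the same dose) will be compared". For the method it names one approach, applied to bundle participants and historical controls at P<.05: "using the log-rank test (to compare the survival distributions of the 2 groups, and these will be calculated using the Kaplan-Meier estimator". It does not mention unequal test schedules or interval censoring.

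The section on the Prospective Study sets the bundle group's schedule: "We will repeat the INR of participants every 2-4 days until stability is reached (2 consecutive INRs are in the target range". Dense testing has a minimum length: "If stability is reached before the 14th day, we will continue to closely monitor the patient for the first 14 days". It goes on longer if stability has not been reached. After stability and one further INR a week later, "participants will continue to follow-up according to the local standard of care".

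Control INRs are taken from clinical records for the first three months (Retrospective Review of Patients' Clinical Records). No testing interval is given for them. The limitations in the Discussion do not mention testing frequency.

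**The concern.** An INR that enters range between two tests is recorded as in range at the later test. Kaplan-Meier and log-rank treat that date as the exact event date. The endpoint also needs a second in-range test at the same dose, so sparse testing can delay or lose an event whose INR has already come into range.

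In the bundle group, the rule that ends dense testing (two successive in-range INRs) is almost the endpoint itself. These participants are watched closely until about the moment the event is seen. Nothing in the article says this of the controls.

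At stake is a secondary efficacy claim, tested at the 5% level, in a study whose findings are meant to shape a larger multisite trial.

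**Working it through.** **Plan's own figure.** There is none for this outcome; the sample size was set for TTR. The check asks how often the stated log-rank test favours the bundle when INR behaviour is identical in both groups.

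**Inputs from the article.** Bundle testing every 2-4 days; event dated at the first of two in-range tests; log-rank at two-sided 5%; 152 prospective and 304 retrospective participants (Sample Size and Power Calculations; Table 1 gives 330 retrospective).

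**Assumptions.** The control interval, which is not stated and was varied; the INR model; a constant dose. Follow-up is 84 days.

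**Rough size of the delay.** If INR enters range at a random point between tests g days apart and stays there, the mean recording delay is g/2.
- Bundle, g = 3: 3/2 = 1.5 days.
- Control, g = 7: 7/2 = 3.5 days, an artificial lag of 3.5 − 1.5 = 2 days.
- Control, g = 14: 14/2 = 7 days, an artificial lag of 7 − 1.5 = 5.5 days.

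**Log-rank test with identical INR behaviour.** The table shows the share of trials significant in favour of the bundle (nominal 2.5%). Model A: INR enters range at a Weibull time (median 10 days, shape 1.3) and stays; 300 runs. Model B: log INR fluctuates with autocorrelation around a rising mean, range 2-3, and the event is the first of two consecutive in-range tests; 200 runs. The Monte Carlo standard error is at most √(0.25/200) = 3.5 percentage points.

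| Control interval (days) | Model A | Model B |
|---|---|---|
| 2-4 (equal) | 5% | 1.5% |
| 3-6 | 9% | 61% |
| 4-7 | 22% | 88% |
| 5-9 | 48% | 100% |
| 7 | 94% | 99% |
| 7-14 | 96% | 100% |
| 14 | 100% | 100% |

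Apparent medians at weekly control testing are 11.6 (bundle) against 14.0 days (control) in Model A, and 10.5 against 16.2 days in Model B. At 7-14 days, Model B gives 10.5 against 24.2.

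**Other assumed INR models.**
- Lognormal entry time (log-SD 0.8), staying in range, 200 runs, control tests about every 7, 10 and 14 days: 35%, 77% and 99% with a true median of 12 days; 18%, 39% and 82% with 20 days. A repeat gave 29%, 72% and 98%, and 18%, 46% and 75%, with 2-2.5% under equal schedules.
- Further fluctuating-INR settings: 49-81% at 3-6 days and 98-100% at 5-9 days, against 3-8% under equal schedules.

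At roughly weekly control testing the rate thus runs from 18% to 100%. Within Model A alone, replacing a 5-9-day spread by a fixed seven-day grid, with the same mean interval, moves it from 48% to 94%.

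**Does interval censoring cure it?** In Model A an interval-censored Weibull test does: 3-9% false positives, mean hazard ratio 0.99-1.01. With fluctuating INR, taking first entry into range as the event and dropping confirmation, it does not (60 runs per setting, standard error up to √(0.25/60) = 6.5 points):
- weekly controls: 22-92% falsely favour the bundle, hazard ratio 1.14-1.45;
- 7-14-day controls: 75-100%, hazard ratio 1.31-1.95;
- equal testing: 2-7%.

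A separate set of runs gave 38-65% at 5-9 days and 85-100% at 7-14 days. Dense testing catches brief entries into range that sparse testing misses, and interval censoring assumes there are none.

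**The case against.** **Control testing may have been frequent.** The article gives no interval, and controls first treated in hospital may have had many early INRs. This stands: a reader might infer that controls were tested only at routine visits, but that is an inference. It limits the size more than the direction. In the lognormal model (true medians 12 and 20 days), controls tested every 2-4 days for 7 days and then about fortnightly still gave 92% and 80%. Dense to day 14 and then fortnightly gave 37% and 53%; dense to day 7 and then weekly, 21% and 18%. The bias goes only if controls were tested about as often as the bundle group until the event.

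**Part of the difference may be real.** The study estimates the effect of the bundle as a whole, and frequent tests allow earlier dose correction. This also stands. A reader might infer that a significant result would show no gain in speed at all; the documents do not support that. Yet dense testing is not among the five components listed in the Introduction, and the Point-of-Care Testing section speaks of faster results, not more tests. The log-rank test cannot divide real gain from earlier detection.

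**The same-dose condition was not simulated.** The study team proposes dose adjustments as INRs come in every 2-4 days. More dose changes could delay qualification in the bundle group and offset some of the bias. This is unresolved.

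**Conclusion.** The concern holds in conditional form. The article itself fixes the definition, the test and the bundle group's schedule, so this is not a detail left to an analysis plan. If controls were tested less often, the stated comparison dates their events later under identical INR control, and a significant result could not be read as faster anticoagulation.

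The size depends on the control testing interval, on how INR fluctuates and on the same-dose rule, none of which the article lets one pin down. A reader might conclude that significance for the bundle is close to guaranteed. That is true only in some settings: in the models where INR stays in range, the false-positive rate is 9% at 3-6-day control testing and as low as 18% at about weekly testing.

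The outcome is secondary, and the primary TTR comparison does not use this test. The matter should be fixed, but it does not undermine the primary analysis.

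**What to change.** 1. Report INR testing intervals by group, for example over days 1-14 and from day 15 to week 12.
2. Make the between-group comparison on a common test grid. One way is to thin each bundle participant's INRs to a testing pattern observed in the controls, apply the same event definition to both groups, and repeat over many draws. Another is to compare the proportion in range at fixed days, using one window for both groups. Thinning equalises detection while keeping any real gain from earlier dose correction.
3. Give an interval-censored analysis as support only, stating that it assumes INR stays in range after entry and only partly removes the bias.
4. Keep the present Kaplan-Meier and log-rank comparison as descriptive, with this limitation stated.

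**Cost.** Some precision is lost by discarding bundle-group tests, and there is a little more analysis work. Thinning can match the control pattern only where bundle tests are at least as dense, which is less sure after care is handed back. No new data are needed, since INR measurements over the first three months are collected in both groups. The article reports analysis under way in February 2023, so the rule should be set before this comparison is seen, or labelled post hoc if it already has been.
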